### Sample size calculation

2.8

We aim to recruit a total of 1,000 participants, of whom we expect approximately 40% will be Māori (based on current figures and expected acceptability of the research protocol). This sample has been calculated to ensure that there is sufficient statistical power to detect a 7% absolute reduction in the 30-day readmission risk in the intervention group for all children and a 12% absolute reduction in the 30-day acute readmission risk for Māori. Sample size calculations are based on a two-tailed 0.05 level of significance with 80% power. We assume that the acceptability of participation will be similar for Māori and non-Māori.

We will measure differences between the intervention and control groups in the primary endpoint (readmission risk) controlling for age, sex, residing in Hamilton, socioeconomic deprivation (NZiDep), and RA responsible for conducting the intervention. Analyses of the primary endpoint will be stratified by ethnicity.

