### Primary endpoint

2.13

The primary endpoint is the relative risk of an acute hospital readmission in the 30 days following discharge for intervention group patients compared with control group patients (Hypothesis 1). The relative risk of readmission rather than readmission rate ratio was chosen as the primary endpoint because risk (probability of readmission within specified period) is easier to measure as it just requires counting the first time a patient is readmitted. By only counting the first readmission we avoid patients with large numbers of readmissions having a disproportion impact on the endpoint measure. This also simplifies statistical analysis. We have included the hazard ratio of readmission as a secondary endpoint (see below).

We will measure ethnic-specific differences in the primary endpoint measures and differences according to a 30-day^2^ readmission risk for Māori and non-Māori patients (combined).

To determine the superiority limit for the purposes of sample size calculations it was considered that the Harti programme should deliver at least a 7% absolute decrease in overall readmission risk as this would be both clinically meaningful for tamariki and whānau and financially meaningful for the hospital. Furthermore, we have designed the study so that it has power to detect a 12% absolute decrease in the 30-day risk of readmission for the Māori population. It is not powered to detect differences in risk of readmission between Māori and non-Māori tamariki.

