### Data handling and monitoring

2.23

Analysis will be performed on an intention to treat basis. That is, endpoints will be compared for the two groups as defined from the point of randomisation to intervention or control group. For the primary endpoint, participants who are readmitted multiple times from each group will be included in the analysis only for the first (valid) occasion on which they are readmitted in the 12 months following the index admission.

Bivariate analyses comparing groups will test for statistical significance using the Chi Square test for differences in proportions. For the length of stay secondary endpoint where a difference in medians is to be tested, the Mann–Whitney *U* test will be used.

Although the randomised design is expected to yield balanced intervention and control groups in a study of this size, logistic regression analysis will be used for the primary and secondary endpoints to control for important confounding variables and to facilitate the assessment of interaction variables that increase or decrease the efficacy of the Harti tool. Statistical significance will be tested at the alpha level of 0.05. We will control for the false discovery rate in the secondary endpoints using the Benjamini–Hochberg method (39).

The study is not powered to detect ethnic differences in the impact of the intervention (effect modification). However, we will nevertheless conduct exploratory tests for effect modification with ethnicity (Māori/non-Māori), gender (male/female excluding other), and deprivation (as a dichotomised variable) using the Breslow Day test for homogeneity of odds ratio, and standard maximum likelihood methods (likelihood ratio tests) based on binomial regression models. We will assume an additive interaction for these analyses and report the relative excess risk due to interaction (RERI) where this is significant effect.

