## Discussion

3

The Harti development and research process aligns to Kaupapa Māori Theory through the prioritisation of Indigenous development and aspirations, the use of tikanga and mātauranga in the development of the intervention, and by our partnership approach with Māori and system stakeholders across the spectrum of programme design, implementation, and evaluation. At the same time our protocol aligns with the requirements of a robust RCT, and we have existing ethical approval and registration.

A universal approach to health care provision has failed to address ethnic inequities in Aotearoa New Zealand (40, 41). While the authors recognise that Māori-specific interventions are also necessary, and the universal versus targeted discussion an important one, in this RCT they wanted to test whether the Harti tool was an important addition in the paediatric ward for all children, as well as enhancing the outcomes specifically for Māori (on the background of greater need). As such, the potential for the findings of this proposed research to be translated into Māori health gains is high. Tamariki Māori have more to gain from the Harti programme than non-Māori children due to greater need, hence the Harti programme is expected to contribute toward decreasing the unjust and pervasive health inequities that exist between Māori and non-Māori New Zealanders, particularly for children. We aim to measure the opportunities for holistic care to reduce hospitalisation rates as our primary outcome, as well as a wide range of secondary outcomes and we have determined an appropriate sample size to ensure that we can understand the risk of hospitalisation as well as the rate of supports provided.

The need for Māori led holistic care that takes a whānau ora approach in addressing the determinants of health, health protective factors, and health risk factors is not limited to child health alone and the Harti approach could be used in multiple areas of Māori health need. In addition, while we aim to undertake a local intervention in the Waikato region of Aotearoa/New Zealand, there is important relevance for our processes and findings across regions and in a wide range of policy settings.

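### The interaction contrast (RERI) is reported only where significant, so its estimate and interval are withheld when the test is inconclusive; low severity, because the analyses are exploratory

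*Protocol article*

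**What the plan says.** Section 2.23 (Data handling and monitoring) first states a limit: "The study is not powered to detect ethnic differences in the impact of the intervention (effect modification". It then says that "we will nevertheless conduct exploratory tests for effect modification with ethnicity (Māori/non-Māori), gender (male/female excluding other), and deprivation (as a dichotomised variable" using the Breslow-Day test and likelihood ratio tests from binomial regression models. It closes with the reporting rule, which takes the interaction to be additive and undertakes to "report the relative excess risk due to interaction (RERI) where this is significant effect". The significance level stated earlier in that section is general: "Statistical significance will be tested at the alpha level of 0.05".

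Section 2.13 (Primary endpoint) repeats the limit for ethnicity: "It is not powered to detect differences in risk of readmission between Māori and non-Māori tamariki".

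Sections 2.8 and 2.13 also plan ethnicity-specific analyses of the primary endpoint, and attach no significance condition to them. No comparable stratified output is stated for gender or deprivation. Nowhere does the article say that the RERI or its interval appears when the test is not significant.

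**The concern.** The clause is a stated reporting rule, not a detail left open. It lets a test that the authors expect to be uninformative, at least for ethnicity, decide whether an estimate is shown. This has two consequences. An inconclusive test leaves out the interval that would show how large an interaction is still compatible with the data. And an estimate that clears a significance threshold at low power is, on average, too far from zero.

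The contrast has a bearing on the trial's rationale. The Discussion expects that "Tamariki Māori have more to gain from the Harti programme than non-Māori children due to greater need". The interaction estimate with its interval is the summary that speaks most directly to that expectation, on the additive scale the plan itself chose. For gender and deprivation, the RERI is the only effect-modification estimate the article mentions.

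**Working it through.** **Inputs from the article.** Total 1,000, about 40% Māori (400 Māori, 600 non-Māori), allocated 1:1. Detectable reductions are 7 points overall and 12 points in Māori (section 2.8). "Sample size calculations are based on a two-tailed 0.05 level of significance with 80% power". No 30-day control risk and no expected non-Māori effect are given, so both are assumptions below. Household clustering and covariates are ignored.

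**Step 1: the plan's own sample size.** Use n per arm = [1.96·√(2p̄q̄) + 0.8416·√(p₁q₁ + p₂q₂)]² / d² and solve for the control risk.
- All children, d = 0.07: risks 0.229 and 0.159 give (1.0961 + 0.4688)² / 0.0049 ≈ 500 per arm, or 1,000 in total.
- Māori, d = 0.12: risks 0.304 and 0.184 give (1.1905 + 0.5062)² / 0.0144 ≈ 200 per arm, or 400 in total.

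The stated size is therefore coherent at control risks of 22.9% overall and 30.4% in Māori. These imply (0.2291 − 0.4 × 0.3042)/0.6 = 17.9% in non-Māori.

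**Step 2: an assumed interaction.** If 12 points in Māori and 7 overall were both true, the non-Māori reduction would be (0.07 − 0.4 × 0.12)/0.6 = 0.0367. The additive contrast is then 0.12 − 0.0367 = 0.0833.

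**Step 3: power for the risk-difference contrast.**
- Variance = 0.304×0.696/200 + 0.184×0.816/200 + 0.179×0.821/300 + 0.1423×0.8577/300 = 0.00271, so SE = 0.0520.
- z = 0.0833/0.0520 = 1.60. Power = Φ(1.60 − 1.96) ≈ 36%.
- The smallest significant estimate is 1.96 × 5.2 = 10.2 points, already above the true 8.3.
- The mean of the significant estimates is about 13.7 points, or 1.65 times the truth (2,000,000 normal draws).
- The contrast detectable with 80% power is (1.96 + 0.8416) × 5.2 ≈ 14.6 points.

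**Step 4: the RERI itself.** With usual-care non-Māori as reference, RERI = RR₁₁ − RR₁₀ − RR₀₁ + 1 = (0.184 − 0.1423 − 0.304 + 0.179)/0.179 = −0.465. In 400,000 simulated trials with a delta-method Wald test, power was 26% and significant estimates averaged 1.9 times the truth. Power is thus lower on this scale than for the risk-difference contrast.

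**Step 5: the odds-ratio scale.** Breslow-Day works on this scale, and the text does not say which test decides whether the RERI appears. At the same risks the log odds ratios are −0.661 and −0.273, a difference of 0.388 with SE 0.327. So z = 1.19 and power is about 22%.

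**Step 6: range (risk-difference contrast).**

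| Modifier | True contrast | Assumed control risks | Power | Mean exaggeration |
|---|---|---|---|---|
| Ethnicity, 400/600 | 8.3 points | 15–30% | 35–43% | 1.5–1.7 |
| Ethnicity, 400/600 | 5 points (12 v 7) | 20–30% | 16–20% | 2.3–2.6 |
| Even split, 500/500 (assumed for gender or deprivation) | 8.3 points | 15–30% | 32–55% | 1.3–1.7 |
| Even split, 500/500 | 5 points | 15–30% | 15–24% | 2.0–2.7 |

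An extreme case, at the Step 1 control risks, is 12 points in Māori and none in non-Māori. Power is then 62% for the risk-difference contrast and 51% for the RERI, with exaggeration of 1.3 and 1.4. That case implies only 0.4 × 12 = 4.8 points overall, not 7.

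**The case against.** The case against has several parts, and most of them stand as limits on the point.

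- **Ethnic results are shown anyway.** The Māori and non-Māori primary effects are planned unconditionally. If they come with intervals, a reader can approximate the unadjusted contrast from two nearly independent strata. This stands. A reader might infer from the clause that real differences by ethnicity will mostly go unreported, but the article does not support that. Only the RERI is conditional, and test results are not said to be withheld.
- **The plan does not equate non-significance with no difference.** This also stands. It labels the tests exploratory and twice states the lack of power for ethnic differences. That a null test would be presented as absence of effect modification is an inference, not something the article says.
- **The lack-of-power statement concerns ethnicity only.** Correct. For gender and deprivation, low power is calculated here under an assumed even split.
- **The 8.3-point interaction is constructed.** Correct. The 7 and 12 points are detectable differences, not a joint forecast of true effects, and the control risks are back-solved.
- **The full plan may list more output.** That would be a fair answer to an omission. Here the article fixes a rule, and nothing in it restores the estimate.

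None of this removes the core. Calling an analysis exploratory does not justify selecting its estimates by p-value. A p-value alone does not show what size of interaction remains possible.

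**Conclusion.** The point holds in a narrow form and is of low severity. Section 2.23 makes reporting of the RERI conditional on significance. For ethnicity this withholds the interaction contrast and its interval, but not the stratum effects. For gender and deprivation it may leave no effect estimate at all.

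Under the assumed scenario, the risk-difference contrast would go unreported about 64% of the time (100 − 36) and the RERI about 74% (100 − 26). Those shown would average about 1.65 and 1.9 times the truth. These figures rest on the back-solved control risks, the implied 3.7-point non-Māori effect, independent observations and Wald tests. That contrasts would usually go unreported ceases to hold for contrasts well above 8.3 points, and at the lowest assumed control risk with an even split (55% power). The primary conclusion, the sample size and trial conduct are unaffected.

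**What to change.** Replace the conditional clause in section 2.23 with: 'The RERI (or the interaction on the risk-difference scale) will be reported with its 95% confidence interval for ethnicity, gender and deprivation whether or not it is significant, as an exploratory result; a non-significant test will not be read as absence of effect modification.'

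The cost is one sentence in the plan and up to three more rows in a results table. No further data are needed.

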### Measures taken to avoid bias

2.24

There is a large risk of contamination or a spill over effect—meaning the control group could get some of the intervention. This could happen for example if the nurses caring for control patients included some of the Harti tool screening questions in their assessments—more so than they normally would. The Hawthorne effect could also contaminate the project, meaning that just having this project happening may lead to better assessment and documentation for control patients. To mitigate the effect of contamination we will remove all Harti tool resources from the ward and stop it's use 6 months before the study starts. We hope this will give enough time for staff to get used to not doing a Harti assessment and to forget the individual questions; there is a high turnover of staff on the wards also so many working during the trial will have never used the Harti tool. We are working to ensure that Harti tool questions are not included into the design of new patient assessment forms. We will explain that a study is taking place but not go into detail for staff and we will not mention the Harti tool. Instead, we will emphasise the patient satisfaction component of the study. During the study period, the RA will keep all documentation, even the blank forms—confidential so as not to contaminate the ward environment.

To maintain blinding and concealment, the only person on the ward who will know explicitly what status the child has, is the RA. The child and whānau may be able to guess from the intervention but will not be told explicitly which group they are in. Results of the intervention assessment will be kept off the ward. As all patients will be consented and given the whānau satisfaction questionnaire by the RA, other ward staff will see the RA sitting with every admitted child and whānau. They may be able to tell who gets an intervention because the RA will spend longer with those who get the intervention than s/he does with those who are randomised to the control group and just get consented and the Mārama satisfaction with care survey. However, contamination is not expected to influence outcomes unduly. The following roles/steps will be blinded to treatment allocation; the person reviewing the notes of control and intervention patients to assess documentation of evidence of assessment, treatment/service delivery and referral/enrolment; the person matching NHIs with service data-bases to assess enrolment and service use; the person matching NHIs with hospital readmission data.

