**Figure d98e549:**
[figure not shown]

Research assistants (RA) were employed for their strengths in cultural safety and ability to engage with whānau Māori. Before the trial begins, training for RAs will take place over weeks with an emphasis on the importance of strong engagement with whānau. This includes learning about the Hui Process for engagement with Māori (31). As part of this, RAs are encouraged to take their time to engage with whānau and make every effort to build trusting relationships and whakamana or recognise the prestige of whānau. Staff engagement training also includes discussions on the importance of whānaungatanga, which is a practice of connecting and establishing respectful relationships. The importance of demonstrating manaakitanga, or showing respect, generosity and care will also be emphasised throughout training and will be revisited through the length of the project. These values will be embedded in the team at the start of the study and reiterated at every opportunity throughout the project including at team meetings, which will range from daily (during recruitment phases) to weekly in other phases.

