### Randomisation procedure

2.7

Randomisation will proceed according to a strict simple (non-stratified) protocol, following consenting, using the Qualtrics™ Survey software which uses the Mersenne Twister algorithm to determine allocation to intervention or control group. The RA will not reveal allocation to the participant, nor will anyone else. The only other person who will have access to group allocation data is the Study Manager.

The RA will continue with the Harti tool or inform usual care participants that they will return to go over the final short satisfaction with hospital experiences Mārama survey before they are discharged.

Because the intervention is whānau/family focussed, study contamination will occur if members of the same household are allocated to different intervention groups. Thus, for any child where another sibling or tamariki/child living in the same household has previously been consented and randomised in the trial, the subsequent child will be allocated to the same intervention group as their household member.

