### Intervention procedure

2.10

The intervention will consist of a 24-section tool with screening questions and follow-up protocols for each question in accordance with the process shown in Figure 2. Intervention group patients and their whānau are invited to go over the Harti tool with the RA and provided with an information and activity booklet (whānau booklet). After engagement, RAs will go through the Harti tool on a tablet. RAs will read out questions in order and fill in answers for participants, in some cases participants may view questions and select responses themselves, if they prefer. The RA will follow established protocols to follow up on any identified areas of need. For example, if a child is not enrolled with a particular service, the RA will offer to assist with enrolment; if the patient or another child present or at home is identified to have a sore throat, then Rheumatic Fever prevention protocols will be followed. RA's will have equipment (cell phones and an iPad) to enable referrals and enrolments to take place at the bedside or in the interview room. The Harti RA will be trained in delivering high quality smoking cessation interventions for whānau and safe sleep devices including Pēpi Pods will be made available. If the whānau are not sure of the child's enrolment status (anecdotally a common occurrence), the Harti RA will match the patient’s National Health Index (NHI) number with selected databases and double check for access or check enrolment with the service over the phone or directly, e.g., oral health services.

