### Whānau satisfaction with care

2.16

Hypothesis 2 examines the difference in satisfaction with hospital experience between the intervention and control groups. This will be measured using the first seven questions from the Mārama real-time survey. Two questions have been added for the purposes of this research: one on the responsiveness to whānau needs, the other on whether a holistic approach was employed (Figure 3). An tenth open-ended Mārama question will also be asked and analysed. The responses will be scored on a 5-point Likert Scale ranging from Strongly Disagree to Strongly Agree (1 point for the former, 5 for the latter), so the total possible score range for someone answering all questions is from 9 to 45 which will be scaled to a range of 0–100 to accommodate cases where one or more questions is not responded to. The responses will be provided by the child’s primary care-giver.

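### The unblinded RA role that delivers the Harti session also gives the satisfaction survey, leaving Hypothesis 2 open to a differential courtesy bias

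*Protocol article*

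**What the plan says.** All references are to the protocol article.

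- **Who delivers the intervention.** Section 2.10: "Intervention group patients and their whānau are invited to go over the Harti tool with the RA". The RA then follows up the needs found, including bedside referrals and enrolments.
- **Who knows the allocation.** Section 2.24: "the only person on the ward who will know explicitly what status the child has, is the RA".
- **Who gives the survey.** Section 2.24 says that all patients are "given the whānau satisfaction questionnaire by the RA". Section 2.7 says that after randomisation the RA either goes on to the Harti tool or will "inform usual care participants that they will return to go over the final short satisfaction with hospital experiences Mārama survey".
- **How RAs are trained.** Section 2.3.1 asks them to "make every effort to build trusting relationships".
- **What is scored.** Section 2.16 uses seven Mārama questions plus two added for this study, "one on the responsiveness to whānau needs, the other on whether a holistic approach was employed". The child's main caregiver answers on a 1–5 agreement scale, and the total is rescaled to 0–100.
- **The target.** Table 2, Hypothesis 2, expects a score 5% higher in the intervention arm, without saying whether this is absolute or relative.
- **Who is blinded.** Section 2.24 lists the notes reviewer, the person matching service databases and the person matching readmission data. It accepts that whānau may guess their arm and that RAs spend more time with intervention families.

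**The concern.** Hypothesis 2 rests on a caregiver's opinion, collected by a role that knows the allocation and has supplied the intervention. Having RAs give the survey in both arms makes the procedure alike but not the relationship behind it. One arm answers to a team that has just worked through 24 topics and arranged practical help, while the other has had less contact and none of that help. The two added items overlap in topic with what the session is meant to provide.

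Section 2.24 considers contamination and the Hawthorne effect but not response bias in this outcome. Section 2.2 calls the trial observer-blinded, which does not describe how Hypothesis 2 is collected. Satisfaction is one of the four research questions in the Introduction, so a positive result is likely to be cited. Randomisation does not remove a bias that arises after allocation, and a larger sample only estimates the biased difference more precisely.

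**Working it through.** **1. RA contact by arm**

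| Contact | Intervention | Usual care |
|---|---|---|
| Approach and consent using relationship-building values (2.9) | yes | yes |
| Baseline form on household, housing and deprivation (2.5) | yes | yes |
| 24-section tool, follow-up, referrals and enrolments (2.10) | yes | no |
| Satisfaction survey given by the RA role (2.7, 2.24) | yes | yes |

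The arms differ only in the third row, and that difference is what could bias the comparison.

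**2. The scale.** Nine items scored 1 to 5 give 9 × 1 = 9 to 9 × 5 = 45, which reproduces the range in section 2.16. The raw span is 45 − 9 = 36, so one category on one item is 100/36 = 2.78 points on the 0–100 scale.

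**3. The target on that scale.** The plan gives no control mean, so both readings are shown.
- Absolute: 5 points = 0.05 × 36 = 1.8 raw points, and 1.8/9 = 0.20 category per item.
- Relative, with an assumed control mean of 60 to 95: 0.05 × 60 = 3.0 to 0.05 × 95 = 4.75 points. These are 1.08 to 1.71 raw points, or 0.12 to 0.19 category per item.

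**4. What shift would equal 5 points.** Suppose a share f of intervention caregivers answers one category higher, the controls do not move, and nobody is held back by the top of the scale.
- On all nine items: f × 9 × 2.78 = 25f. Setting 25f = 5 gives f = 20%.
- On the two added items only: f × 2 × 2.78 = 5.56f. Setting 5.56f = 5 gives f = 90%.

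A small general shift therefore reaches the target, whereas the two added items alone need nearly every caregiver to move.

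**5. What would be statistically significant.** Take 1,000 participants split 1:1 (sections 2.2 and 2.8), assume complete responses, and compare means. The smallest significant difference is about 1.96 × SD × √(2/500).

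| Assumed SD | Smallest significant difference (points) | Power for 5 points |
|---|---|---|
| 10 | 1.2 | >99% |
| 15 | 1.9 | >99% |
| 20 | 2.5 | 98% |
| 25 | 3.1 | 89% |

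Under these assumptions, a bias well below the target could still give a significant result.

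**The case against.** The strongest reply is that the problem is partly shared between arms and its size is unknown. Much of that stands.

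- **Same person.** A reader might infer that the individual who delivered the session always gives the survey. The text supports this for the role only. Section 2.8 adjusts for the RA who conducted the intervention, which implies several RAs, and section 2.6 allows the survey up to two weeks after discharge without saying who gives it then.
- **Interview.** A reader might infer that the questions are read aloud. The article does not state the mode, and the full protocol may.
- **Control contact.** It would be wrong to say that control families had nothing but a consent conversation. They are approached with the same values and complete the baseline form, so some courtesy towards RAs is common to both arms and cancels.
- **Item content.** The wording is in Figure 3, which is not shown. A rise on the two added items may be a genuine effect, since the intervention aims at exactly those things.
- **Direction.** Bias in favour of the intervention is probable but not certain. A long assessment with sensitive topics could also burden some families.
- **Masking.** RA contact with every family is part of how section 2.24 hides the arm from ward staff, so a change has a price.

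These points limit the claim but do not answer it. The longer contact and practical help remain confined to one arm, and the plan states no safeguard for this outcome.

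**Conclusion.** The concern holds as a risk of bias in Hypothesis 2. The allocation-aware role that delivers the session also gives the survey, and survey administration is not among the blinded steps. A difference in scores could reflect a real gain in satisfaction, courtesy towards the RA team, or both, and the design cannot tell them apart.

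The size is illustrative. The target is 0.20 category per item if absolute, or 0.12 to 0.19 if relative with an assumed control mean of 60 to 95. A 5-point gap needs 20% of intervention caregivers to move one category on every item, with no movement in controls and no ceiling. A high control mean would restrict the shift.

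A reader might infer that courtesy bias will by itself produce the 5% difference. The documents do not support that: they show only that it could. Nor do they support doubt about the primary endpoint on this ground, because readmissions come from hospital data matched by a blinded person.

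**What to change.** In sections 2.6, 2.16 and 2.24, state that:

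1. in both arms the caregiver completes the survey privately on the existing tablet, with the RA nearby but not viewing the answers. Section 2.10 already lets this happen for the Harti tool: "in some cases participants may view questions and select responses themselves, if they prefer";
2. where help is needed, it comes from an RA who did not deliver that family's session, if one is on shift;
3. the same timing rule applies in both arms;
4. the mode, the timing and who assisted are recorded;
5. the seven standard items are reported separately from the two added ones.

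The cost is protocol wording and a small roster rule, with no new staff because the second item applies only when another RA is present. Item non-response may rise, and masking from ward staff may weaken slightly if RAs sit less with families. Some response bias would remain, since families cannot readily be blinded to a bedside assessment. Section 2.4.1 places recruitment between July 2018 and December 2019. If collection is complete, separate reporting of the two item groups, with mode and timing where recorded and a stated limitation, is still possible.
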